## Assessment of intensity

The assessment of severity will be determined by the investigator and recorded on the case report form (CRF) AE page and SAE form according to the investigator’s best clinical judgment, taking into consideration various factors such as the subject’s report, the physician’s observations, and the physician’s prior experience. The investigator will assess the individual (S)AE severity using the following scale:

| **mild:** | Event is easily tolerated and does not cause any real problem to the patient. It does not interfere with routine activities. |
| --- | --- |
| **moderate:** | Event interferes with routine activities. |
| **severe:** | It is impossible for the patient to perform routine activities. |

## Assessment of causality

The determination of the likelihood that the study intervention caused the AE (causality assessment) will be provided by the investigator. The assessment of causality will be determined by the investigator and recorded on the CRF AE page and SAE form according to the investigator’s best clinical judgment. The following questions should be considered in determining the relationship between the study intervention and the AE:

- Was the study intervention administered?
- Was there another obvious cause of the AE?
- What was the temporal sequence of the onset of the AE relative to the study intervention?
- Was the AE consistent with the known pattern of response to study intervention?
- Could the subject‘s clinical state, environmental or toxic factors, or other modes of therapy administered to the subject have caused or modified the AE?
- Did the AE resolve or improve after study intervention was discontinued or reduced?
- Did the AE remain the same or worsen after study intervention was discontinued or reduced?
- If the subject was re-exposed (rechallenged), did the AE recur or worsen upon re-exposure? Did the AE not recur or improve with re-exposure? (Clinical judgment should be used for determining if rechallenge is appropriate.)

Taking into account any of the above factors, the Investigator will assess the causality of the individual AEs using one of the following:

| **unassessable:** | Due to insufficient information the causality cannot be assessed. |
| --- | --- |
| **unlikely:** | The adverse event may easily be explained with sufficient other information that there is no causality with the study intervention. |
| **possible:** | The adverse event follows a reasonable temporal sequence after administration of the intervention or a known response pattern to the suspected intervention. It could readily have been produced by the patient´s clinical state, environmental or toxic factors, or other modes of therapy administered to the patient. |
| **probable:** | The adverse event follows a reasonable temporal sequence after administration of the intervention or a known response pattern to the suspected intervention. It could not be reasonably explained by the known characteristics of the patient´s clinical state, environmental or toxic factors, or other modes of therapy administered to the patient. It disappears or decreases on cessation or reduction in dose of study intervention. |
| **certain:** | The adverse event follows a reasonable temporal sequence after administration of the intervention, disappears after cessation or dose reduction of the intervention and occurs again on reexposition. |

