### Side effects and possible adverse events

The processing of anxiety, inner conflict or topics linked to paranoid ideation during therapeutic intervention could lead to a temporary destabilization of the patient with increasing dynamics of delusions, hallucinations and formal thought disorder or depression. Possible side effects/ complications would be exacerbation of psychotic symptoms, suicidal ideation, suicide attempts, suicide and aggression.

Adverse effects may also result from the treatment in a group setting. Hoffmann et al. therefore created a list of indications and contraindications for group psychotherapy (see also [24] and [25]). Participants should be able to adhere to the framework agreements (such as dates, duration). Psychotic symptoms of other patients might impose a burden on participants, and problems may arise from unfavourable group dynamics that might not always be resolved by the therapist. However, the specific technique of art therapy as well as the inpatient setting are suitable to recognise and minimise risks. Art therapy is less demanding with respect to the mental stability of patients compared to other group therapies, because it allows for a unique triadic interaction between patient, therapist and work of art. Art therapy offers a creative space that can bear protective properties. A lot of time is spent working silently, and adverse tendencies in group dynamics can be effectively controlled by the therapist. However, individual adverse reactions to the group setting or as a result of high emotional intensities evoked by self-exploration in the creative process can not be completely excluded.

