### Treatment schedule

Patients are treated in groups of up to five people. In the pilot study twelve sessions of art therapy will be performed, offered twice weekly. A session lasts 90 minutes.

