# Termination and Subsequent Treatment

## Premature termination of subjects / discontinuation / withdrawal

For the following reasons the patient may be taken out of the trial:

- personal wish of the participant
- withdrawal of consent
- loss of contact, move
- newly manifested exclusion criteria
- repeated adverse events
- serious adverse event
- significant violations of protocol

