# Statistical Analysis

## Determination of Sample Size

No usable effect sizes are reported in the literature as a necessary basis for sample size estimation. Therefore, no sample size estimation will be performed. This pilot trial is conducted to generate data and to estimate effect sizes to prepare for a future, larger efficacy trial.

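### Section 9.5 makes improvement on stopping a fixed condition of the *probable* grade, which irreversible or one-off events and events starting after the last session cannot meet (minor)

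*Protocol*

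**What the plan says.** Section 9.5 (Assessment of causality) has the investigator choose one of five grades for each adverse event: unassessable, unlikely, possible, probable or certain.

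- *Possible*: a reasonable time sequence or known response pattern, and "It could readily have been produced by the patient´s clinical state, environmental or toxic factors" or other therapy.
- *Probable*: the same time or pattern condition, no reasonable explanation by those other factors, and then "It disappears or decreases on cessation or reduction in dose of study intervention".
- *Certain*: a reasonable time sequence, and the event "disappears after cessation or dose reduction of the intervention and occurs again on reexposition".
- *Unassessable* is reserved for insufficient information, and *unlikely* for events that other information easily explains.

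Section 5.1.1 lists the harms that the protocol itself expects might occur: "Possible side effects/ complications would be exacerbation of psychotic symptoms, suicidal ideation, suicide attempts, suicide and aggression". Section 5.1.2 sets out the course: "In the pilot study twelve sessions of art therapy will be performed, offered twice weekly". Section 5.4 requires the intervention to be stopped at once in severe adverse reactions and leaves continued participation to a case-by-case decision. Section 8.1 makes withdrawal after a serious adverse event optional, in a list that opens "For the following reasons the patient may be taken out of the trial".

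**The concern.** The condition about stopping is written into *probable* without a qualifier such as where applicable. The list of questions earlier in section 9.5 does treat re-exposure conditionally, but the grade definitions drop that condition. A scale of this form suits a drug reaction that fades when the drug is withdrawn. Two of the harms listed in section 5.1.1 are not of that kind, and they are the gravest ones.

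Section 3 gives preliminary data on safety as an aim of the pilot, and section 2.2 says that evidence on harmlessness is insufficient. Causality is recorded for each event. With about 30 patients (section 3.2) and a purely descriptive safety analysis (section 13.2.4), the grade given to a single serious event could colour the safety summary. A rule that keeps a suicide out of the two upper grades, whatever the evidence, tilts that summary towards reassurance.

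**Working it through.** The protocol gives no figure to reproduce here, so the check sets the grade definitions beside the listed harms.

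**Inputs.** The grade definitions come from section 9.5, the five harms from section 5.1.1, the course from section 5.1.2, and the stopping and continuation provisions from sections 5.4 and 8.1.

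**Step 1: can the stopping condition be met at all?** It is met by cessation or by dose reduction. The protocol describes no dose levels, so reduction has no defined meaning. Cessation does: section 5.4 provides for it. The condition can therefore be observed for any event that has a course over time and begins while sessions are still running.

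**Step 2: apply it to each listed harm.**

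| Harm (5.1.1) | Can it fade after stopping? | *Probable* reachable? | *Certain* reachable? |
| --- | --- | --- | --- |
| Psychotic exacerbation | Yes | Yes | Only if the patient returns and it recurs |
| Suicidal ideation | Yes | Yes | Only if the patient returns and it recurs |
| Aggression | Yes | Yes | Only if the patient returns and it recurs |
| Suicide attempt (single) | No, a completed act | No, on the literal wording | Would need a second attempt after re-exposure, and the first still has no course that could fade |
| Suicide | No | No | No |

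Blocked from *probable*: 1 outright (suicide) + 1 in practice (single attempt) = 2 of 5. Not blocked: 5 − 2 = 3 of 5.

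**Step 3: events after the last session.** The intervention runs for 6 weeks and follow-up ends at week 12, which leaves 12 − 6 = 6 weeks in which an event of any type can begin after cessation. Section 9.7 also asks for reports of serious events after the study that can reasonably be linked to the intervention. For all of these there is no later stopping against which to judge improvement, so *probable* and *certain* cannot be met literally.

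**Step 4: which grade is left?** Take a blocked event with a plausible time sequence.

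- If the patient's clinical state could readily have produced it, *possible* fits and there is no gap.
- If no other reasonable explanation exists, *possible* does not fit, because its text says one is readily available. *Probable* fails on the stopping condition alone. *Unlikely* does not fit, because no other information explains the event. *Unassessable* does not fit, because information is not what is lacking.

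In the second branch no grade applies as written. The investigator must still choose one, and every grade the wording leaves open is weaker than the evidence supports.

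**The case against.** The strongest reply is that the gap is small and little depends on it. Participants are inpatients in acute psychotic episodes (section 6.2), so clinical state will usually be a ready alternative cause and *possible* will fit. Section 9.5 relies on the investigator's best clinical judgment rather than a mechanical rule. Section 9 puts all adverse events into the analysis, section 9.7 requires serious events to be reported immediately and deaths within 24 hours, and the SUSAR definition in section 9.3 names no causality grade. A suicide during the study would be reported and counted whatever its label.

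Most of this stands, and it sets the severity. It does not remove the defect: judgment guides the choice among grades but does not rewrite their definitions, and here the definitions leave no suitable grade.

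Three stronger readings are tempting, and the documents do not support them.

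- A reader might infer that a fixed 12-session course can never show improvement on stopping or recurrence. The criterion accepts cessation as well as reduction, section 5.4 provides for stopping and for a decision on continuing, and withdrawal under section 8.1 is optional. Re-exposure matters only for *certain*, and a demanding top grade is a legitimate choice.
- A reader might count aggression as a third blocked harm. A single isolated act is arguable, but section 5.1.1 lists aggression, and section 4.2 groups it with agitation and hostility, as a state that can rise and subside.
- A reader might conclude that the pilot will report few or no probable harms by construction. Three of the five listed harms can be graded *probable*, so this does not follow.

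**Conclusion.** The point holds in a narrow form and is minor. As worded, *probable* and *certain* are out of reach for suicide and a single suicide attempt (2 of the 5 listed harms) and for any event that starts after the last session. Where such an event also lacks another reasonable explanation, it falls between *possible* and *probable*, and its relatedness would be under-graded.

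This rests on reading the three conditions for *probable* as all required, which is how they are written, and on treating a single attempt as a completed act with no continuing course. The protocol gives no expected event frequencies, so the number of events affected cannot be estimated. In this population it is likely to be small. What is affected is the recorded relatedness of rare, grave events in a pilot that aims to provide safety data. Their reporting during the study and their inclusion in the analysis are not affected.

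**What to change.** Add to section 9.5, and to the CRF adverse event page:

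- Improvement on cessation is required for *probable* only where it can be assessed.
- For irreversible or one-off events, and for events that begin after the last session, *probable* rests on a reasonable temporal sequence and the absence of another reasonable explanation.

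*Certain* can stay as it is. Removing the references to dose reduction, which has no defined meaning for this intervention, is optional tidying and does not affect the point.

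The cost is one or two sentences and a matching CRF note, with no change to treatment, sample size or analysis. The downside is that some events may be graded as more strongly related than under the present wording.

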## Recording of (Serious) Adverse Events

The investigator will closely monitor each patient for evidence of intolerance of the study intervention. All adverse events occurring during the course of the study must be reported on the appropriate pages of the Case Report Forms and followed up until they have disappeared.

## Reporting of Serious Adverse Events (SAE) and Suspected Unexpected Serious Adverse Reactions (SUSAR)

**SAE:**

All serious adverse events will be reported immediately to the sponsor by the investigators according to GCP-V § 12. SAE which need not be reported: surgeries or other inpatient residences known *before* inclusion in the trial. Serious adverse events which occur after conclusion of the study and can still reasonably be considered to be related to the study intervention are also to be reported. Any death during the study has to be reported to the sponsor within 24 hours. In cases where a pathologist's report may substantially assist in clarifying the event an autopsy should be performed. In addition biopsy materials, blood samples and specialist's reports should be provided if considered useful.

**SUSAR:**

The sponsor must report all suspected serious unexpected adverse reactions occurring during the course of the study to the Ethics Committee, Competent Authority (if applicable) and investigators within 15 days, according to GCP-V § 13. In case of death, the SUSAR has to be reported within 7 days, and further relevant information has to be provided within the next 8 days.

All transferred data have to be pseudonym. Reporting of SUSARs require unblinding of the individual.

# Documentation

## Case Report Forms (CRF)

All assessed data will be documented in paper CRF.

## Investigator´s Site File

All essential documents, such as signed informed consents, will be filed in an Investigator´s Site File and archived for at least 10 years (according to ICH GCP chapter 8).

## Archiving the Data at the Trial Centre

According to GCP guidelines, the sponsor ensure that all study documents such as the study files and patient documents are archived for at least 10 years after the end of the study or its premature termination. Administrative documents (communication with ethics committee, copies of protocol, amendments, patients' identification log, signed informed consent forms) will be archived for 10 years at the site. Data will only be deleted with the authorisation of the sponsor. All data and documents will be made available if requested by relevant authorities. Patient medical records will be archived according to current regulations (Krankengeschichtenverordnung, KgVO) for at least 15 years.

# Quality Management

All investigators will perform the study according to the study protocol. Protocol deviations will be documented with reasons. Regular meetings will be held to discuss the trial progress.

## Monitoring

There will be no external monitoring for this pilot study.

# Data Management

All data will be documented and saved in pseudonym form. Each patient is identified by a study patient ID, neither including the full birth date, nor initials. The investigators document the allocation of the patient's name to the ID in a patients' identification log. Only the principal investigators, study physicians and other study responsibles have access to this log.

## Data Collection / Case Report Forms

Data will by collected via paper-CRF forms (CRF). CRFs will be stored separately from the patients' identification log. CRFs will be filled in by ball-pen, pencils are not allowed. Corrections can be made by crossing out an entry, correct onformation is given directly next to the previous entry, the study responsible/physician will sign the correction with his name, date and reason for correction. Data fields left open due to missing information have to be commented on.

The CRFs will be archived for 10 years.

## Data Processing

After form reading and data export, data management includes plausibility, consistence and range checks with possible following data corrections. Non-plausible or missing entries can be corrected in accord with the study physician; correction protocols will be stored together with the CRF.

The validated data base will be saved as "KUSS_date". The clear data base will be called as “closed”. The logging of all steps of data management procedures and corrections will be saved in (repeatable) scripts for PASW 18.0.

## Generation of Pseudonym

The pseudonym will neither contain initials nor birth-dates, and is composed as follows: "KUSS_randomisation number".

# Statistical Analysis

## Determination of Sample Size

No usable effect sizes are reported in the literature as a necessary basis for sample size estimation. Therefore, no sample size estimation will be performed. This pilot trial is conducted to generate data and to estimate effect sizes to prepare for a future, larger efficacy trial.

## Statistical Analysis

### Hypotheses

**Primary Hypothesis:**

- HH: The administration of 12 sessions of psychodynamic group art therapy in addition to standard treatment is associated with a greater reduction in positive, negative and depressive symptoms and with better psychosocial functioning compared standard treatment alone.

**Secondary Hypotheses:**

The administration of 12 sessions of psychodynamic group art therapy in addition to standard treatment is associated with....

- NH1: higher overall satisfaction with care,
- NH2: higher quality of life,
- NH3: a higher expectation of self-efficacy and a more internal locus of control,
- HN4: higher measures of cognitive empathy and emotional awareness, i. e. increased mentalising ability

### Definition of Population for Analysis

The intent to treat analysis will be executed with all available patient’s data independent of dropouts and protocol violations. The per protocol analysis will be accepted only for the patients who finished the trial in accordance with the study protocol (valid cases).

### Analysis of Primary und Secondary Objectives

The primary objective is to determine differential changes of symptom ratings (SANS, SAPS, CDSS) and psychosocial function (GAF score) from baseline. Measurement points are the examinations post-treatment (6 weeks) and at follow-up (12 weeks). Changes are compared between intervention and control groups under consideration of possible confounding variables (repeated measures ANOVA/ ANCOVA, two-tailed level of significance: alpha=0.05).

Secondary objectives and the respective endpoints (satisfaction with care, self-efficacy, social cognition) will be analysed in the same manner. Statistical calculations will be carried out using PASW 18.0.

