**The following data are documented as possible confounding variables:**

- Demographics (age, gender, education, genetic background, age and gender of siblings, marital status, housing, vocational status, assisted living/ community psychiatric care)
- Illness characteristics (year/ age of first manifestation, course of illness, number of episodes, number of psychiatric hospitalisations, course of antipsychotic treatment, non-pharmacological treatments, suicidality, familiy history
- Neurocognition (Multiple choice vocabulary test, MWT-B; Wisonsin card sorting test, WCST; Auditory verbal learning test, AVLT)

**Structured clinical interviews** for DSM-IV (SCID I and SCID II items referring to antisocial personality disorder) are performed to confirm inclusion and exclusion criteria with respect to diagnosis.

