## Clinical examinations and trial-related deviations of clinical practice

Clinical examinations and symptom ratings, blood tests, pregnancy testing, urine drug screening and ECG belong to necessary routine examinations in schizophrenic patients. Patients with first manifestation of psychotic illness undergo extensive clinical diagnostics including MRI and EEG. Taking a detailed history of the patient and repeated diagnostic interviews also belong to clinical routine. Structured clinical interviews, personality and some of the neuropsychological tests are usually administered according to clinical indication in routine diagnostic procedures. However, the majority of tests and ratings (quality of life, self-efficacy, social cognition) are exclusively performed for scientific purposes. Randomised allocation of treatment is a deviation from clinical practice, the risk of which is minimised by additional visits and standardised ratings of side-effects.

**Table 1:** time schedule for study examinations

| **Instrument** | **Visit 0:**  **Pre-trial** | **Visit 1: Baseline** | **Randomisation**  **and 6 weeks**  **intervention**  **phase** | **Visit 2:**  **Post-treatment**  **(within 7 days after end of intervention)** | **Visit 3: Follow-up**  **(within 7 days after 12 weeks follow-up date)** |
| --- | --- | --- | --- | --- | --- |
| **Informed consent** | x |  |  |  |
| **Inclusion criteria** | x |  |  |  |
| **Demographics** | x |  |  |  |
| **SCID I** | x |  |  |  |
| **SCID II (APD)** | x |  |  |  |
| **SANS/ SAPS** |  | x | x | x |
| **CDSS** |  | x | x | x |
| **GAF** |  | x | x | x |
| **MWT-B** |  | x |  |  |
| **WCST** |  | x |  |  |
| **AVLT** |  | x |  |  |
| **ZUF-8** |  |  | x |  |
| **MSQoL** |  | x | x | x |
| **FKK** |  | x | x | x |
| **RME** |  | x | x |  |
| **LEAS** |  | x | x |  |
| **Medication dose** |  | x | x | x |
| **Documentation of adverse events** |  |  | continuously | x |  |

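### Section 13.2.3 analyses change from baseline without naming the outcome's own baseline score as covariate, and its model does not fit ZUF-8, which is measured only once

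*Protocol*

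**What the plan says.** Section 13.2.3 of the protocol defines the outcome as a change: "The primary objective is to determine differential changes of symptom ratings (SANS, SAPS, CDSS) and psychosocial function (GAF score) from baseline". The measurement points are week 6 and week 12. It continues: "Changes are compared between intervention and control groups under consideration of possible confounding variables", and gives the method as "repeated measures ANOVA/ ANCOVA, two-tailed level of significance: alpha=0.05".

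The covariates are not listed there. Section 3 uses the same term to head a list: "The following data are documented as possible confounding variables". The list has three groups:

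- Demographics: "Demographics (age, gender, education, genetic background, age and gender of siblings, marital status, housing, vocational status, assisted living/ community psychiatric care".
- Eight items on the history of the illness, running from its onset and course through earlier care to suicidality and family history.
- Neurocognition: MWT-B, WCST and AVLT.

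No baseline SANS, SAPS, CDSS or GAF score is on the list, and 13.2.3 does not mention one as a covariate.

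For the secondary endpoints, with satisfaction, self-efficacy and social cognition given in brackets, 13.2.3 says only that they "will be analysed in the same manner". The synopsis lists t-tests, ANCOVA and repeated-measures MANCOVA, without assigning them to endpoints. Section 13.2.6 only refers back to 13.2.3.

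**The concern.** In a small randomised trial with a scale measured before and after treatment, the baseline value of that scale is usually the covariate most worth including. Here it is collected on every primary scale but not named, while attention goes to a long list of other variables. Plain repeated measures ANOVA is one of the two permitted methods. In it, the group-by-time contrast between baseline and a later visit is exactly an unadjusted comparison of change scores.

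Sections 3 and 13.1 say that the pilot is to supply effect sizes and sample-size inputs for a larger trial. Its main product is therefore a set of estimates and their precision. An analysis that discards precision and leaves chance baseline differences in the estimate harms that product directly. A covariate set with no selection rule adds uncertainty about which estimate will be reported.

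The ZUF-8 problem is of another kind: the prescribed analysis needs a baseline that the visit schedule does not provide.

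**Working it through.** The protocol gives no power, effect size, SD or correlation (section 13.1), so there is no figure of its own to reproduce.

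**Inputs.** 15 patients per arm, about 30 in total (sections 3.1 and 3.2); two-sided alpha 0.05 (13.2.3). Assumed: correlation r between baseline and follow-up of 0.3 to 0.7; equal SDs at both times; all 15 per arm evaluable; for power, a true difference of 0.8 SD.

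**Candidate covariates.** 9 demographic + 8 illness + 3 neurocognitive = 20.

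**Variance at one visit, in units of SD².** Change score: 2(1−r). Baseline-adjusted ANCOVA: 1−r². Ratio: (1−r²)/[2(1−r)] = (1+r)/2.

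| r | change | ANCOVA | ratio | CI width, √ratio | equivalent sample, 1/ratio |
| --- | --- | --- | --- | --- | --- |
| 0.3 | 1.40 | 0.91 | 0.65 | 0.81 | 1.54 |
| 0.5 | 1.00 | 0.75 | 0.75 | 0.87 | 1.33 |
| 0.7 | 0.60 | 0.51 | 0.85 | 0.92 | 1.18 |

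Estimating one covariate costs a factor of about 27/26. The ratios become 0.675, 0.779 and 0.883. At r = 0.9 the ratio is 0.987, so the gain has almost gone.

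**What this means at 15 per arm (normal approximation).** Power for 0.8 SD rises from 46% to 63% (r = 0.3), from 59% to 72% (r = 0.5) and from 81% to 87% (r = 0.7). The difference detectable with 80% power falls from 1.21 to 0.98, from 1.02 to 0.89 and from 0.79 to 0.73 SD.

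**Chance imbalance.** The standard error of the baseline difference is √(2/15) = 0.365 SD. An imbalance above 0.5 SD in either direction corresponds to |z| > 0.5/0.365 = 1.37, which has probability about 17% on any one scale. A change-score comparison carries a fraction (1−r) of the imbalance into the estimate. For a 0.5 SD imbalance that is 0.35, 0.25 and 0.15 SD at r = 0.3, 0.5 and 0.7.

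**Visit schedule (Table 1, section 6.6) against 13.2.3.**

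- SANS/SAPS, CDSS, GAF, MSQoL, FKK: baseline, post-treatment, follow-up. Change exists at both later visits.
- RME, LEAS: baseline and post-treatment. Change exists at one later visit.
- ZUF-8: post-treatment only. Neither a change nor a group-by-time term can be estimated.

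The table's columns are partly misaligned in the text available. The ZUF-8 row still has a single mark and an empty baseline cell, while rows in the same layout have two or three marks.

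**The case against.** The strongest reply is that silence is not exclusion. ANCOVA is named in both 13.2.3 and the synopsis and may well be meant to include baseline. The exact covariates are commonly left to a statistical analysis plan, which may exist. This stands in part: the protocol cannot be said to rule baseline adjustment out. But it fixes change as the outcome, allows plain ANOVA, and describes the covariates in terms that do not include the baseline score.

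It can also be said that the variance ratio is for one visit, while the plan has two. If both are averaged and all correlations equal r, the variances are 1.5(1−r) for change and (1−r)(1+2r)/2 for ANCOVA. The ratio is then (1+2r)/3: 0.53, 0.67 and 0.80. The conclusion does not weaken.

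On ZUF-8, the first secondary hypothesis in 13.2.1 concerns a level of satisfaction, not a change, and the synopsis mentions t-tests. A workable analysis is therefore within reach. It is only not the one that 13.2.3 prescribes.

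A reader might infer three further things, which the documents do not support:

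- That about 20 covariates enter the model. The items are recorded as candidates, and no section says that all of them, or any fixed number, are fitted. Residual degrees of freedom worked out for such a model describe an analysis that nobody has specified.
- That the comparison is adjusted for post-randomisation drug dose. "Medication dose" is a row in Table 1 and is not on the section 3 list, whose nearest item is the course of antipsychotic treatment, under illness history.
- That RME and LEAS cannot be analysed. Two time points are enough for a change or for ANCOVA; only a week-12 result is absent.

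**Conclusion.** This is a free improvement with one small internal contradiction attached.

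The plan leaves open an unadjusted change-score analysis of its primary scales. Baseline-adjusted ANCOVA would have 65% to 85% of that variance at a single visit for r between 0.7 and 0.3 (the lower r, the larger the gain). This is worth as much as 18% to 54% more patients, before the small cost of one degree of freedom. The size rests on the assumed r and on equal SDs at both times. The direction depends little on them: with unequal SDs s0 and s1, the change-score variance exceeds the ANCOVA variance by (s0 − r·s1)², which is never negative. The gain becomes negligible only when r is very high.

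The open list of 20 candidates for about 30 patients is a reason to name the covariates in advance. It does not show over-adjustment.

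The conflict between 13.2.3 and Table 1 over ZUF-8 is real but minor. It affects one secondary endpoint and has an obvious remedy.

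**What to change.** Reword section 13.2.3, or the statistical analysis plan if there is one, before unblinding:

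- **Primary scales (SANS, SAPS, CDSS, GAF):** analyse the scores at Visits 2 and 3 by arm, with the baseline value of the same scale as covariate.
- **Secondary scales with a baseline:** the same model for MSQoL and FKK at Visits 2 and 3, and for RME and LEAS at Visit 2.
- **Further covariates:** limit them to a short list of baseline variables named in advance.
- **ZUF-8:** replace the change or repeated-measures analysis with a between-arm comparison at Visit 2, reported with a 95% confidence interval.

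The cost is wording only. No visit, instrument or patient is added, and every value needed is already scheduled in Table 1.
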